### Statistical methods

Sample size calculation was performed for the primary outcome. The median overall survival in the comparator arm was estimated at 18 months. In order to detect a HR of 0.70 with 80% power and a 5% two-sided significance level, a total of 252 events (deaths) are needed. The number of events is expected to be reached after the inclusion of 378 patients in 36 months, with analysis planned 18 months after the last patient has been randomized. Sample size calculation was performed using East software (East 6 [2020]. Statistical software for the design, simulation and monitoring clinical trials. Cytel Inc., Cambridge MA).

The primary analysis will be performed by intention-to-treat. Survival estimates will be obtained using the Kaplan–Meier method. The stratified log-rank test will be used to test the difference between the treatment arms. Treatment effect will be estimated using a stratified Cox proportional-hazards model. Subgroup analysis according to baseline characteristics will be performed for age, sex, serum CA 19–9 level, tumor location, WHO performance status, tumor size, and venous contact. A p value < 0.05 is considered to indicate statistical significance.

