## Methods

### Trial design

The PREOPANC-3 trial is an international, multicenter, phase 3, RCT initiated by the Dutch Pancreatic Cancer Group (DPCG). Patients with resectable pancreatic cancer are randomized to neoadjuvant mFOLFIRINOX followed by surgery and adjuvant mFOLFIRINOX (intervention; arm 1) or to surgery and adjuvant mFOLFIRINOX (comparator; arm 2) (Fig. 1). Randomization is performed centrally in a 1:1 ratio using the minimization technique with World Health Organization (WHO) performance status (0 vs. 1), serum carbohydrate antigen 19–9 (CA 19–9) level (< 300 vs. ≥ 300 U/ml), and center as stratification factors.

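### The primary survival analysis specifies no covariate adjustment, although prognostic baseline values are recorded: a missed gain of about 1 to 7 points of power, not an error

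*Protocol article*

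**What the plan says.** All places are in the Protocol article.

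- **Statistical methods, primary analysis.** By intention to treat, the arms are compared with a stratified log-rank test, and "Treatment effect will be estimated using a stratified Cox proportional-hazards model". The strata are not named and no covariates are listed.
- **Statistical methods, subgroups.** Age, sex and CA 19-9 level are listed for subgroup analysis, together with "tumor location, WHO performance status, tumor size, and venous contact".
- **Trial design.** "Randomization is performed centrally in a 1:1 ratio using the minimization technique". The factors are WHO performance status (0 or 1), CA 19-9 split at 300 U/ml, and center. These are the only stratification factors named anywhere, so reading them as the analysis strata is an inference.
- **Statistical methods, sample size.** "In order to detect a HR of 0.70 with 80% power and a 5% two-sided significance level", "a total of 252 events (deaths) are needed". These deaths are expected "after the inclusion of 378 patients in 36 months, with analysis planned 18 months after the last patient has been randomized". Also: "The median overall survival in the comparator arm was estimated at 18 months".

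**The concern.** In a proportional-hazards setting, leaving prognostic covariates out of the comparison lowers power at a fixed number of deaths, even when the arms are perfectly balanced on them. Minimization does not recover this loss. The trial already plans to use the relevant baseline values for subgroups, yet the stated primary test and estimate draw on none of them beyond the strata.

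The design has almost no reserve above 80%, so power that needs no extra patients, deaths or follow-up is worth having. It is credible only if the covariates are fixed before outcomes are seen.

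**Working it through.** **1. The plan's own figures.** Inputs from Statistical methods: HR 0.70, two-sided 5%, 80% power, 1:1, 378 patients, 36 + 18 months, comparator median 18 months. (1.960 + 0.842)² = 7.849.

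- Freedman deaths: 7.849 × (1.70/0.30)² = 252.04, matching the stated 252.
- Schoenfeld deaths: 4 × 7.849/(ln 0.70)² = 246.8, so 247.
- Power at 252 deaths: Freedman Φ(√252 × 0.30/1.70 − 1.960) = Φ(0.841) = 80.0%; Schoenfeld Φ(√252 × 0.3567/2 − 1.960) = Φ(0.871) = 80.8%.
- Expected deaths, exponential survival without dropout: P(death) = 1 − (e^(−18λ) − e^(−54λ))/(36λ). Comparator, λ = ln 2/18: 0.729. Intervention, 0.70 × λ: 0.606. 189 × (0.729 + 0.606) ≈ 252.4 (from unrounded values).

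The design reproduces without any adjustment.

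**2. Power with adjustment.** The documents give no prognostic strengths, so a range was assumed and simulated: 378 patients, analysis at the 252nd death, 5,000 trials per scenario. Further assumptions: half the patients at performance status 1, about 31% at or above 300 U/ml, no center effect, no dropout, and balance within strata standing in for minimization. The planned test is taken as a log-rank test in four strata (performance status × CA 19-9 split). The adjusted test is the treatment term of a Cox model with the same strata plus continuous log CA 19-9 and an index of the other baseline values. The conditional HR was set so that the overall HR is about 0.70.

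| Assumed prognosis | Log-HR, status 1 vs 0 | Log-HR per SD: CA 19-9, other index | Conditional HR | Planned test | Adjusted test | Gain (points) |
|---|---|---|---|---|---|---|
| Weak | 0.2 | 0.10, 0.15 | 0.694 | 80.1% | 81.3% | 1.2 |
| Moderate | 0.3 | 0.20, 0.30 | 0.682 | 81.5% | 84.5% | 3.0 |
| Moderate-strong | 0.3 | 0.25, 0.40 | 0.673 | 82.0% | 86.8% | 4.8 |
| Strong | 0.4 | 0.30, 0.50 | 0.661 | 82.7% | 90.0% | 7.3 |

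The Monte Carlo standard error of one power figure is about √(0.82 × 0.18/5000) = 0.5 point. Both tests were run on the same simulated trials. Under the null (moderate prognosis) the adjusted test rejected in 4.6% of trials.

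A second simulation used five covariates with a combined log-hazard SD of 0.28, 0.42 and 0.57. It gave 80, 81 and 82% for the planned test against 82, 85 and 89% adjusted, with type I error of 4.9 to 5.5%.

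**3. Gain as deaths.** Extra deaths ≈ 252 × [((1.960 + z_adj)/(1.960 + z_plan))² − 1], with z the normal quantile of each power:

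- Weak: (2.849/2.805)², about 8.
- Moderate: (2.975/2.857)², about 21.
- Strong: (3.242/2.902)², about 62.

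**4. Share due to CA 19-9.** Adding continuous log CA 19-9 alone moved power from 80.1 to 80.1, 81.5 to 82.0, 82.0 to 82.3 and 82.7 to 83.2%, that is by 0 to 0.5 point. Across all settings tried, the gain was at most about one point. The reason is that a split of a normal variable at 0.5 SD (31% above) keeps φ(0.5)²/(p(1 − p)) = 0.352²/(0.3085 × 0.6915) = 58% of its variance.

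**The case against.** The strongest reply is that nothing here is wrong. A stratified log-rank test with a stratified Cox estimate is valid, fits the randomization, and meets its power target. Covariate lists, functional forms and missing-value rules often sit in an analysis plan, and that plan is not shown. Adjustment in a Cox model also changes the estimand: in the moderate case an overall HR of 0.70 corresponds to a conditional HR of about 0.68, so the difference between them is not bias in the planned estimate. Finally, being a subgroup variable does not make a value prognostic, and venous contact is limited by eligibility to 90 degrees or less.

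Much of this stands. It makes the point an improvement rather than a correction, and it argues against making a conditional HR the primary result. It does not remove the point, because the article states the primary test and model, and a later supportive adjusted model would leave that primary test unchanged.

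Three stronger readings are tempting, and the documents do not support them:

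- **The trial is underpowered.** If 0.70 is held as the conditional HR, simulated power of the planned test falls to 78.5% (weak) and 70.7% (strong), against 79.1% and 79.9% adjusted. The article gives 0.70 no such meaning: it stands beside an arm median and reproduces from an unadjusted formula.
- **Several points of power are certainly lost.** That needs moderate or stronger prognosis, which is assumed.
- **Splitting CA 19-9 at 300 wastes most of its information.** The split is stated for the minimization only, and step 4 shows that its cost would be small.

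**Conclusion.** The concern holds as a missed efficiency gain. The stated primary analysis is valid and has its 80% power at 252 deaths. With the overall HR near 0.70, adjustment would add about 1 point of power if the baseline values are weakly prognostic, 3 if moderately so, and 5 to 7 if moderately strong to strong. Nearly all of this comes from covariates other than CA 19-9, with no material inflation of type I error.

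The size depends on the assumed prognostic strengths and on analysis strata of performance status and CA 19-9 without center, which the article leaves open. The adjusted figures come from a Cox model; the adjusted log-rank test recommended below was not itself simulated.

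**What to change.** - Keep the planned strata, the 378 patients and the 252 deaths.
- Before any outcome data are seen, prespecify a short covariate list (age, log CA 19-9, tumor size, tumor location, venous contact), the form of each, and a simple rule for missing values that uses neither arm nor outcome.
- Make a covariate-adjusted stratified log-rank test the primary test. It keeps the marginal hypothesis. Confirm its gain by simulation when the list is fixed.
- Report the covariate-adjusted stratified Cox HR, labelled as conditional, beside the planned stratified Cox HR.
- Keep the planned unadjusted stratified log-rank test as a supportive analysis.

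The cost is analysis-plan wording, some extra programming, and a second, conditional HR that must be explained to readers. The documents do not say how complete the baseline values will be, so the missing-value rule has to be written without that knowledge.

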## Discussion

Here, we describe the study protocol for the international, multicenter, phase 3, randomized PREOPANC-3 trial that compares perioperative mFOLFIRINOX with adjuvant mFOLFIRINOX in patients with resectable pancreatic cancer.

Currently, surgical resection followed by adjuvant therapy with mFOLFIRINOX is the standard of care for patients with resectable pancreatic cancer based on the PRODIGE 24/CCTG PA.6 trial [5]. In this trial, the median overall survival in patients treated with adjuvant mFOLFIRINOX was 54.4 months compared with 35.0 months in patients treated with adjuvant gemcitabine. In the long-term analysis, these results were confirmed with a 5-year survival of 43.2% with mFOLFIRINOX compared to 31.4% with gemcitabine [15].

To date, two phase 3 RCTs that compared neoadjuvant with adjuvant therapy for resectable and borderline resectable pancreatic cancer are available. In the Japanese Prep-02/JSAP-05 trial, 364 patients were randomized to neoadjuvant gemcitabine and S-1 chemotherapy, surgery and adjuvant S-1 or to upfront surgery with adjuvant S-1 [16]. Overall survival was better with neoadjuvant therapy (HR 0.72; 95% CI, 0.55 to 0.94; *P* = 0.015). In the Dutch PREOPANC trial, 246 patients were randomized to neoadjuvant gemcitabine-based chemoradiotherapy, surgery, and adjuvant gemcitabine or to upfront surgery with adjuvant gemcitabine [17, 18]. After a median follow-up of 59 months, improved survival was observed with neoadjuvant chemoradiotherapy (HR 0.73; 95% CI, 0.56 to 0.96; *P* = 0.025). Furthermore, a recent meta-analysis of only RCTs including 938 patients found improved survival outcomes with gemcitabine-based neoadjuvant therapy compared with upfront surgery and adjuvant therapy [8]. None of the patients in these trials received adjuvant mFOLFIRINOX as they were designed before publication of the PRODIGE 24/CCTG PA.6 trial. Neoadjuvant mFOLFIRINOX is already the standard of care for patients with borderline resectable pancreatic cancer based on a patient-level meta-analysis and several phase 2 studies [19–21]. However, data regarding the use of neoadjuvant mFOLFIRINOX in patients with resectable pancreatic cancer is limited. The phase 2 SWOG S1505 trial that compared perioperative mFOLFIRINOX (6 cycles neoadjuvant; 6 cycles adjuvant) with perioperative gemcitabine/nab-paclitaxel (3 cycles neoadjuvant; 3 cycles adjuvant) in 102 patients with resectable pancreatic cancer found a median overall survival of 23.2 months and a resection rate of 73% in patients treated with mFOLFIRINOX [22]. In the three-arm, phase 2, PANACHE01-PRODIGE48 trial, 153 patients were randomized to 4 cycles of neoadjuvant mFOLFIRINOX, 4 cycles of neoadjuvant FOLFOX or to upfront surgery with adjuvant chemotherapy [23]. Patients in the neoadjuvant arms received 8 cycles of adjuvant chemotherapy. One year overall survival was 84.1% with neoadjuvant mFOLFIRINOX, 71.8% with neoadjuvant FOLFOX, and 80.8% with upfront surgery. Resection rates were 74%, 68%, and 81%, respectively. The largest retrospective series of neoadjuvant mFOLFIRINOX in patients with resectable pancreatic cancer included 346 patients from 5 centers in the United States and the Netherlands and found a median overall survival of 31.2 months and a resection rate of 70.5% [24].

Comparison of survival outcomes of neoadjuvant and adjuvant trials is difficult, if not impossible. Adjuvant trials include only patients who have undergone resection. These patients successfully underwent pancreatectomy and recovered adequately to be considered for adjuvant therapy. In addition, adjuvant trials require a recent CT scan and some trials had upper limits for post-resection CA 19–9. In contrast, neoadjuvant trials include patients with resectable pancreatic cancer on imaging. As a result, neoadjuvant trials include patients that are found to have metastases or unresectable disease at surgical exploration, patients who died from surgery, and patients with surgical complications or clinical deterioration precluding adjuvant therapy. A recent meta-analysis of 7 RCTs demonstrated that even in the upfront surgery arm 1 in 5 patients underwent no resection, mostly due to metastatic disease found during surgery [8].

In the PREOPANC-3 trial, patients in the intervention arm are scheduled for 4 cycles of adjuvant mFOLFIRINOX after 8 cycles of neoadjuvant mFOLFIRINOX and resection. The exact benefit of adjuvant chemotherapy after neoadjuvant FOLFIRINOX and resection is unclear. An international cohort study that investigated the value of adjuvant therapy after neoadjuvant mFOLFIRINOX found improved survival only in the subgroup of patients with pathology proven node-positive disease [25]. We chose 12 cycles of mFOLFIRINOX in both arms to balance the total number of scheduled cycles between the treatment arms.

Radiotherapy is not part of the neoadjuvant treatment in the intervention arm. Currently, there is insufficient evidence that neoadjuvant (chemo)radiotherapy improves overall survival when scheduled in combination with neoadjuvant mFOLFIRINOX. A meta-analysis including 512 patients with resectable and borderline resectable pancreatic cancer treated with radiotherapy after FOLFIRINOX found higher R0 resection rates without improved overall survival [26]. In addition, a propensity matched analysis including 300 patients with borderline resectable pancreatic cancer treated with and without radiotherapy found similar overall survival [27]. The recent phase 2 ALLIANCE A021501 RCT also found no survival benefit of mFOLFIRINOX followed by stereotactic body radiotherapy (SBRT) compared with mFOLFIRINOX alone in patients with borderline resectable pancreatic cancer [21].

Accrual is challenging in RCTs that compare perioperative chemotherapy to upfront surgery in patients with pancreatic cancer. In a recent meta-analysis, only three of the seven trials were able to complete accrual [8]. The DPCG has demonstrated with the PREOPANC and PREOPANC-2 trials that it can reach timely and complete accrual [17, 28].

Currently, two other RCTs compare perioperative with adjuvant administration of mFOLFIRINOX in patients with resectable pancreatic cancer. In the Scandinavian NorPACT-1 trial (NCT02919787), 140 patients were randomized between 2017 and 2021 to 4 cycles of neoadjuvant mFOLFIRINOX followed by surgery and 8 cycles of adjuvant mFOLFIRINOX or to surgery and 12 cycles of adjuvant mFOLFIRINOX. Results are expected by the end of 2022. In the United States, the ALLIANCE A021806 trial (NCT04340141) randomizes 352 patients to 8 cycles of neoadjuvant mFOLFIRINOX followed by surgery and 4 cycles of adjuvant mFOLFIRINOX or to surgery and 12 cycles of adjuvant mFOLFIRINOX.

In conclusion, the PREOPANC-3 trial is designed to compare perioperative mFOLFIRINOX with adjuvant mFOLFIRINOX in patients with resectable pancreatic cancer.

### Trial status

The PREOPANC-3 trial opened for accrual on August 24, 2021 and the first patient was randomized on September 7, 2021. As of January 1, 2023, 16 of the 23 planned hospitals are open for inclusion and 100 patients have been randomized.

## Data Availability

Data sharing not applicable to this article as no datasets were generated or analyzed during the current study.

## Abbreviations

CA 19–9: Carbohydrate antigen 19–9
CEA: Carcinoembryonic antigen
CT: Computed tomography
DPCG: Dutch Pancreatic Cancer Group
DPD: Dihydropyrimidine dehydrogenase
DSMB: Data Safety Monitoring Board
eGFR: Estimated glomerular filtration rate
mFOLFIRINOX: 5-Fluorouracil with leucovorin, irinotecan, and oxaliplatin
G-CSF: Granulocyte colony stimulating factor
GDPR: General Data Protection Regulation
GIST: Gastrointestinal stromal tumor
HR: Hazard ratio
ISGPS: International Study Group of Pancreatic Surgery
NCCN: National Comprehensive Cancer Network
pNET: Pancreatic neuroendocrine tumor
RECIST: Response evaluation criteria in solid tumors
SAE: Serious adverse event
SUSAR: Suspected Unexpected Serious Adverse Reactions
WHO: World Health Organization
